### Intervention description

#### C-THR intervention arm

Component 1 of the *C-THR* intervention utilizes telehealth technology facilitated by a peer counselor to connect participants to on-demand visits with a study physician and clinical psychologist. Technology is available wherever the participant is located and prefers engagement (e.g., SSP, home, shelter, encampment) via a HIPAA-compliant videoconferencing application, iPads, and headphones for privacy. All study physicians practice medicine through a harm reduction lens and are experienced in HIV prevention and the treatment of SUD. A call schedule across the study physicians will support on-demand access for participants. By incorporating enhanced access to a clinical psychologist, the *C-THR* intervention will also be capable of addressing the estimated 40% of people with SUD who have co-occurring mental health disorders [55] (e.g., post-traumatic stress disorder, depression and anxiety) as well as the participants who have stimulant use disorders. The psychologist will formulate a treatment plan and visit frequency with study physicians as determined by clinical indication(s), and will provide ongoing services including talk therapy and psychotropic medications to address concurrent mental health disorders. This essential component will allow for an evidence-based approach to co-occurring stimulant use disorders which are prevalent in the Miami PWID community [56] to augment emerging pharmacotherapies [57–60].

On-site, culturally appropriate blood draws will be performed at the SSP fixed or mobile sites by a medical assistant/phlebotomist and sent to the lab for testing. Blood will be sent to LabCorp to measure creatinine, and to the Department of Health to be tested for HIV, viral hepatitis, and STIs. The medical assistant/phlebotomist will swab the participants’ throats to test for gonorrhea and chlamydia and will instruct the participants on how to collect a self-swab for rectal gonorrhea and chlamydia in a private bathroom. Urine will be collected for gonorrhea and chlamydia screening, as well. Finally, point-of-care urine tests will assess the presence of buprenorphine or tenofovir.

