### Outcomes

Table 1 shows the primary and secondary outcomes of objective 1. The co-primary outcomes will be engagement in HIV prevention via PrEP and/or via MOUD. PrEP engagement will be measured by intracellular levels of TFV-DP on DBS or abstraction of a cabotegravir injection in the previous 8 weeks. MOUD engagement will be measured by norbuprenorphine or methadone on UDS or abstraction of a naltrexone or buprenorphine injection in the previous 4 weeks.

**Table 1 Tab1:** Primary and secondary outcomes for objective 1

	Definition	Measure
Primary outcome		
HIV Prevention via PrEP	Taking PrEP at 3-, 6-, 9-, and 12-month follow-up	Intracellular levels of tenofovir diphosphate (TFV-DP) by DBS or cabotegravir injection in previous 8 weeks by electronic health record abstraction
HIV Prevention via MOUD	Taking MOUD at 3-, 6-, 9-, and 12-month follow-up	Norbuprenorphine or methadone on UDS or naltrexone or buprenorphine extended-release injection in previous 4 weeks by electronic health record abstraction
Secondary outcomes		
Syringe coverage	Dispensing syringes to cover each injection event	Number of syringes distributed/(number of injections per day × days between exchanges) from SSP administrative data
PrEP Adherence	Taking PrEP at least 4 times per week	TFV-DP level of 700 fmol/punch on DBS for TDF [64]; TFV-DP level of 950 fmol/punch on DBS for TAF[65]
Engagement in HCV treatment	Receiving a prescription for DAA	DAA prescsiption confirmed on electronic health record abstraction
HCV cure (SVR 12)	Initiating HCV treatment and achieving undetectable HCV RNA PCR at least 12 weeks after completion of therapy	Negative HCV RNA PCR (viral load) at least 12 weeks post treatment completion
Treatment of STIs	Receiving treatment for STI after a positive screen	Prescription of appropriate antibiotics (may differ based on allergies) from electronic health record abstraction
Time to harm	Time to: (1) emergency department visit or hospitalization for injection-related infection or overdose; (2) incident HIV infection; (3) incident HCV infection; or (4) death from overdose	(1) Electronic health record abstraction; (2, 3) IDEA test results; (4) electronic health record abstraction or medical examiner database

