Number of harms	Count of (1) emergency department visit or hospitalization for injection-related infection or overdose; (2) incident HIV infection; (3) incident HCV infection; or (4) death from overdose	(1) Electronic health record abstraction; (2, 3) IDEA test results (4) electronic health record abstraction or medical examiner database

Secondary analyses will evaluate positive health behaviors by counts per person per study arm. PrEP adherence will be defined as taking PrEP at least four times per week for men and at least 6 times per week for women as confirmed by TFV-DP levels on DBS. HCV treatment engagement will be defined as receipt of a prescription for DAA. HCV cure will be defined as sustained virologic response at least 12 weeks after completing DAA (SVR 12) and treatment of STIs is defined as receipt of the appropriate antibiotic treatment after diagnosis. Secondary outcomes will also evaluate negative health outcomes or harms by counts per person per study group. Emergency department visits or hospitalizations will be confirmed by participants’ consent for records release and abstraction from Miami area hospitals which have integrated electronic health records. Incident HIV and HCV infections (or reinfections) will be confirmed by positive 4th generation HIV antigen/antibody test and detected HCV RNA, respectively. Death from overdose will be confirmed by hospital record, Miami-Dade County Medical Examiner database search or direct inquiry with the medical examiner. In addition to counts, time to secondary outcomes, both positive and negative, will be compared by study arm.

For objective 2, the primary health economic outcomes will be: (1) implementation and ongoing management costs of the two healthcare models, and (2) short-term cost-effectiveness from the perspectives of the healthcare sector and society. The primary economic outcome will be the incremental cost-effectiveness ratio (ICER) from the healthcare sector and modified societal perspectives. The measure of effectiveness will be quality-adjusted life years (QALYs) and incident HIV infections averted.

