### Sample size

Power analyses were generated using the two-group repeated proportions module in PASS 2020 [68] to compute minimum detectable effect sizes for the proposed primary analysis. The study will include 350 participants equally assigned to the intervention and control groups. We assume that as much as 10% of the sample may drop-out at each follow-up; however, we anticipate better retention due to SSP staff engagement in the study [69]. The expected sample sizes at the four follow-ups are thus 315, 284, 255, and 230. Using these sample sizes and assuming α = 0.025, power = 0.80, and that the proportion with PrEP or MOUD engagement will be 30% of the control arm, we computed the minimum detectable odds ratio (OR) 1.56 and absolute proportion difference (pdiff) of 0.101, assuming that all post-intervention time points are part of the contrast. We varied the within-subject correlation ρ from 0.10 to 0.80. Power for a binomial is lowest when the base-rate (control group) probability (P_0_) is near 50%.

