**Table 3 Tab3:**
[figure not shown]
Assessment schedule

All participants will complete laboratory assessments at screening and at 3-, 6-, 9- and 12-month follow-up assessments. At screening, this will include rapid HIV test by fingerstick and point of care urine screens for tenofovir, buprenorphine, and methadone to determine eligibility. Additional tests at screening include fourth generation HIV test, HCV RNA, STI screens, hepatitis serologies, comprehensive metabolic panel, complete blood count and, as indicated, urine pregnancy test. At baseline and at 3-, 6-, 9- and 12-month follow-up assessments, these will include urine drug screen for buprenorphine/norbuprenorphine and methadone/EDDP (methadone metabolite) and fingerstick DBS to test for both the presence and therapeutic levels of TFV-DP related to the primary outcome, as well as HIV Ag/Ab screen, HCV RNA, HIV/HCV rapid tests, and STI screen (including syphilis via blood and gonorrhea/chlamydia via throat swab, rectal swab, and urine). Additionally, participants in the *C-THR* arm will also have a creatinine assessment at 6 and 12 months.

To confirm primary outcome by medical record abstraction, the electronic health record will be quieried for date of injection of (1) cabotegravir, (2) naltrexone or (3) buprenorphine. A cabotegravir injection in the previous 8 weeks will be considered as having met the primary outcome. A naltrexone or buprenorphine injection in the previous 4 weeks will be considered as having met the primary outcome.

The cost and cost-effectiveness analysis will consist of an economic evaluation of *C-THR* versus non-SSP clinic referral and patient navigation from both the healthcare sector perspective and the modified societal perspective. Specifically, the evaluation will focus on budgetary impact and cost-effectiveness to inform application of *C-THR* locally and nationally. This evaluation will follow recommendations of the 2nd Panel on Cost Effectiveness in Health and Medicine [45], Glick et al. [46] and Drummond [47].

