### Plans for collection, laboratory evaluation and storage of biological specimens for genetic or molecular analysis in this trial/future use

The primary and secondary outcomes for objective 1 will be measured with TFV-DP on fingerstick DBS, buprenorphine/norbuprenorphine or methadone/EDDP (methadone metabolite) on UDS, HIV Ag/Ab screen, HCV RNA, HIV/HCV rapid tests, and STI screen (including syphilis via blood and gonorrhea/chlamydia via throat swab, rectal swab and urine). These laboratory assessments will be completed as routine blood, urine, and throat and rectal swab lab tests, sent to a commercial laboratory or Florida Department of Health, and destroyed according to their procedures.

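### Incident HIV is defined by one positive antigen/antibody test, with no supplementary test and no rule for disagreement with the rapid test done at the same visit

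*Protocol article*

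**What the plan says.** The case rule is in the Outcomes section, in the text after Table 1: "Incident HIV and HCV infections (or reinfections) will be confirmed by positive 4th generation HIV antigen/antibody test and detected HCV RNA, respectively". It is worded as a definition of what counts, and for HIV it names one test.

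Table 1 does not add to it. For incident HIV and incident HCV (items 2 and 3 of both harm outcomes) the measure column gives only "2, 3) IDEA test results; (4) electronic health record abstraction or medical examiner database", with no assay or algorithm.

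Under Plans for assessment and collection of outcomes, the laboratory work at baseline and at each follow-up includes "as well as HIV Ag/Ab screen, HCV RNA, HIV/HCV rapid tests, and STI screen". A rapid HIV test and an antigen/antibody test are therefore both scheduled at every follow-up visit. The section on biological specimens repeats the list. For the C-THR arm, blood goes "to the Department of Health to be tested for HIV, viral hepatitis, and STIs"; the laboratory's testing sequence is not described.

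Incident HIV is used in three places: as one of four components of Time to harm, as one of four components of Number of harms, and in the economic objective, where "The measure of effectiveness will be quality-adjusted life years (QALYs) and incident HIV infections averted".

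**The concern.** The rule attaches the idea of confirmation to a single immunoassay. The comparison with HCV in the same sentence is telling. Rapid HCV tests are also done at each visit, yet an incident HCV case needs detected RNA. The protocol separates a first-line result from a confirming result for HCV but not for HIV.

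The test is repeated four times in people enrolled because they were HIV-negative, so true infections are likely to be few and even a small false-positive rate can matter. Someone with a reactive antigen/antibody result, a negative rapid test and negative supplementary results would, on the literal rule, be an incident infection dated at that visit. That adds one to the harm count and ends harm-free time if no other harm came first. It matters most for infections averted, where HIV stands alone and is not diluted among other harms.

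**Working it through.** **Inputs from the protocol article.** "The study will include 350 participants equally assigned to the intervention and control groups", with up to 10% drop-out assumed at each follow-up and expected sample sizes of 315, 284, 255 and 230 (Sample size).

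**Reproducing the plan's figures.** 350 × 0.9 = 315; × 0.9 = 283.5; × 0.9 = 255.2; × 0.9 = 229.6. These round to the stated numbers, and 230/350 = 66%, the 12-month retention given in the retention section.

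**Number of tests.** 315 + 284 + 255 + 230 = 1,084. With full retention it would be 4 × 350 = 1,400.

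**Person-years.** Average the numbers at the start and end of each quarter: 332.5 + 299.5 + 269.5 + 242.5 = 1,144; × 0.25 = 286. Counting 0.25 years per completed test gives 1,084 × 0.25 = 271, about 5% lower.

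**Assumptions, not in the documents.** Specificity per test of 99.5% to 99.99%; true HIV incidence of 0.5 to 2 per 100 person-years; false-reactive results independent across tests.

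**Formulas.** False positives = 1,084 × (1 − specificity). True infections = 286 × incidence. False share = false / (false + true).

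True infections: 286 × 0.005 = 1.4; 286 × 0.01 = 2.9; 286 × 0.02 = 5.7.

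| Assumed specificity | False positives | False share at 0.5 per 100 | at 1 per 100 | at 2 per 100 |
|---|---|---|---|---|
| 99.5% | 5.4 | 79% | 65% | 49% |
| 99.8% | 2.2 | 60% | 43% | 27% |
| 99.9% | 1.1 | 43% | 27% | 16% |
| 99.99% | 0.1 | 7% | 4% | 2% |

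**Where the two are equal.** Incidence = 1,084 × (1 − specificity) / 286. This is 1.9 per 100 person-years at 99.5%, 0.76 at 99.8%, 0.38 at 99.9% and 0.04 at 99.99%. False positives outnumber true infections only when incidence is below these values. With 271 person-years, 99.5% and 2 per 100, the counts are equal at 5.4 each. Full retention barely moves the comparison: 1,400/350 = 4.0 tests per person-year against 1,084/286 = 3.8.

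**Direction of error.** The false-positive counts are upper estimates at the plan's drop-out. The article places a fourth-generation test at screening and an antigen/antibody test at baseline, so persistently false-reactive people may be found before follow-up. Someone reactive at several visits is also one case, not several.

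**Effect on a between-arm difference.** With equal testing in both arms, false positives cancel on average in a difference of counts but add noise. Treated as Poisson, their between-arm difference has a standard deviation of √2.17 = 1.5 at 99.8%, against 2.9 true infections in the whole trial at 1 per 100.

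**The case against.** The strongest reply is that this is an article, and a supplementary algorithm may sit in the full protocol or with the testing laboratory. That stands in part. A reader might infer that no confirmatory testing takes place; the documents do not show that. But the article does more than stay silent: it states which result makes a case. If the laboratory's algorithm is the real endpoint, the sentence misdescribes it.

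Second, the rule can be read as the laboratory test confirming a reactive rapid test, since both are done at each visit and entry follows that order. The reading is possible, but no text requires a reactive rapid test or says how disagreement is resolved.

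Third, a reader might treat the label in "HIV Ag/Ab screen, HCV RNA, HIV/HCV rapid tests, and STI screen" as a contradiction with the case rule. It is weak evidence. The protocol uses the same word for the urine drug test that defines a co-primary outcome, and elsewhere calls the HIV assay a test.

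Fourth, the consequence is limited. HIV is one of four harm components, no separate between-arm test of HIV is specified, and long-term HIV prevention is projected by a simulation model. All of this stands and limits the weight of the point.

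**Conclusion.** The point holds as a defect in an outcome definition. The article fixes incident HIV at one positive antigen/antibody result, with no supplementary test and no rule for disagreement with the concurrent rapid test, while requiring RNA for HCV.

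Its size is uncertain. Under the assumed ranges, false positives run from about 0.1 to 5.4 against 1.4 to 5.7 true infections, that is, from negligible to more numerous than the true cases. A reader might conclude that false positives will match true infections. The documents do not support that, because they give neither specificity nor incidence, equality is reached in only part of the range, and the counts assume independence despite testing at screening and baseline.

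The effect is confined to two secondary harm outcomes and observed HIV infections averted. The co-primary outcomes are untouched. The correction is worth making because it is cheap and the rule, if followed as written, can count an unconfirmed result as an infection.

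**What to change.** Amend the sentence in the Outcomes section so that, for outcome counting only:

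- an incident HIV infection requires a reactive antigen/antibody result supported by a supplementary antibody test or detectable HIV RNA, and is dated at the first reactive specimen;
- a reactive result with negative supplementary results is not an event;
- the same definition applies to Time to harm, Number of harms and observed HIV infections averted.

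If the testing laboratory already runs such an algorithm, name its final result as the endpoint instead. The change can be made before data lock. The cost is one sentence and retrieval of supplementary results for a handful of participants.

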### Participant timeline

Participant timeline is presented in Fig. 1.

**Fig. 1 Fig1:**
[figure not shown]
RCT study flow

### Sample size

Power analyses were generated using the two-group repeated proportions module in PASS 2020 [68] to compute minimum detectable effect sizes for the proposed primary analysis. The study will include 350 participants equally assigned to the intervention and control groups. We assume that as much as 10% of the sample may drop-out at each follow-up; however, we anticipate better retention due to SSP staff engagement in the study [69]. The expected sample sizes at the four follow-ups are thus 315, 284, 255, and 230. Using these sample sizes and assuming α = 0.025, power = 0.80, and that the proportion with PrEP or MOUD engagement will be 30% of the control arm, we computed the minimum detectable odds ratio (OR) 1.56 and absolute proportion difference (pdiff) of 0.101, assuming that all post-intervention time points are part of the contrast. We varied the within-subject correlation ρ from 0.10 to 0.80. Power for a binomial is lowest when the base-rate (control group) probability (P_0_) is near 50%.

### Recruitment

Participants will be recruited from the IDEA Miami SSP by our racially and ethnically diverse staff that includes peer counselors. For *C-THR*, individuals presenting to the IDEA Miami SSP who are interested in: (1) HIV/HCV testing; (2) PrEP; (3) MOUD; (4) STI screening; (5) treatment of HCV; and/or (6) assessment/treatment for SSTI will be asked if they would like to participate in a research study using technology for PWID-specific preventive healthcare.Via Rapid Testing: The IDEA Miami SSP conducts routine HIV/HCV screening, with opt-out screening offered every 3 months. Individuals who test non-reactive for HIV will be asked if they would like to participate in a research study on using technology for HIV prevention.Community Engagement Team Referral: The IDEA Miami SSP has a community engagement team to provide wrap-around support for PWID using the SSP. Any potential participant seeking the aforementioned medical services may be referred to the study coordinator.Peer Referral: Randomized study participants will be provided an additional $50 incentive for each eligible participant referred to the study who is randomized up to four. Participants who screen fail will be provided an additional $50 incentive for each eligible participant referred to the study who is randomized up to eight.Study Flyer: A flyer and palm card with contact information for the study coordinator will be posted at the SSP, on mobile units, and distributed through street outreach. The flyer may be posted on social media, as well as Reddit forums.Hospitalized PWID: The Severe Injection Related Injury Team at Jackson Health System will refer potentially eligible participants. Participants will be provided a study flyer and referred to the IDEA Miami SSP to sign screening consent. Study procedures will be deferred until the patient is ambulatory at the SSP.

It is anticipated that throughout the recruitment period, encounters for routine HIV/HCV screening, PrEP, MOUD, STI screening/treatment, and/or assessment for SSTI will facilitate identification of 440 participants who could be eligible for the study. Of these, we expect 80% (n = 352) to be eligible for randomization.

For completing the screening process, including quantitative assessment and laboratory analysis, participants will receive $50 total. Participants in both arms will receive $50 per laboratory assessment (at 3, 6, 9, and 12 months) and $50 per quantitative assessment (at 0, 6, and 12 months). Fifteen participants in each arm will participate in in-depth qualitative interviews at study completion and will receive $50 for the interview (at 12 months). Additionally, enrolled participants may refer up to four individuals to the study and receive $50 each if randomized. Total possible compensation will be $600.

## Assignment of interventions: allocation

### Sequence generation

Participants (n = 350) will be randomized by permuted block randomization to *C-THR* or non-SSP clinic referral and patient navigation. All randomizations will be stratified by recruitment site (fixed vs. mobile) and baseline OUD diagnosis (OUD vs. no OUD). Randomization will occur with central control using the REDCap program and will be external to the IDEA Miami SSP to assure a robust and unbiased approach.

### Concealment mechanism

Centralized randomization will occur in REDCap and group assignment will be concealed until randomization.

### Implementation

The study coordinator and the research assistant will enroll eligible participants into the trial for random assignment after approval by the study principal investigator. The statistician will encode REDCap with the allocation sequence which will assign treatment condition after the eligibility REDCap form has been completed by the principal investigator.

## Assignment of interventions: blinding

### Who will be blinded

This clinical trial is unblinded. For a robust and unbiased approach, our randomization procedure is strong with central control external to the study site. All data analysis strategies are pre-specified and the finalized data analysis plan will be confirmed prior to data lock. The data analysis will not be blinded since [name] and [name] are study investigators and performing the analysis. [name] and [name] will, however, be blinded to treatment assignment in conducting their analysis until results are finalized.

